### Quantitative data analysis

Specifically, for Objective #1, we will test the effectiveness of the MDET intervention on clinical outcomes (for example, HbA1C ≤ 7%, LDL-C <2.0 mmol/L) using the generalized linear mixed models (GLMM), which include site as the random effect, time as a fixed effect and the intervention effect. With the GLMM approach, the temporal trends in the effect of the intervention are also evaluated, while the correlations between patients within the same site as well as the variations between sites are accounted for (Hussey *et al.*, 2007)
[46]. The patient-level covariates (for example, age, sex, duration living with diabetes, smoking status) and PCP-level (within sites) covariates (for example, years of practice) will also be included in the model. Hierarchical linear models (HLM)
[49,50] are an important special case of GLMM, and the former name is more commonly seen in the literature for nested data structures (for example, patients at Level 1, PCPs at Level 2 and sites at Level 3). GLMM will facilitate modeling all three level variances in patient outcomes, while utilizing patient variables at Level 1, PCP variables at Level 2 and site variables at Level 3. In addition, we will consider the generalized estimating equations (GEE) approach, which has been suggested to be more robust to misspecification of the variance structure (including. correlations between patients within sites) (Hussey *et al.*, 2007)
[46]. For Objective #2, we will evaluate the effect of the MDET intervention on quality of care delivered to patients (for example, screening for ACR and eGFR) using the GLMM approach, as described for Objective #1, in addition to descriptive summaries (for example, for change in drug dose, PCP years practicing). GLMM will also be used to assess the intervention effect on, for example, the referral rate to DEPs under Objective #3, where the PCPs form the unit of the analyses, and the correlation between PCPs within sites will be taken into account along with the temporal trends of the MDET effects.

For the analyses described above, overall Type I error will be set to 1% (instead of 5%) for all calculations of confidence intervals and for testing the various hypotheses, in order to account for the possible occurrence of false positives due to “multiple testing” (increased chance of finding statistical significance beyond the nominal significance level). Model diagnostic tools and cross-validation methods will be considered for model assessment. Since missing values are unavoidable, these values will be handled with extra caution. Reasons and mechanisms for the missing data points will be explored by various summary statistics as well as graphical displays. Appropriate statistical techniques to handle missing values will be further explored and taken into account in the proposed statistical modeling
[51], (including imputation of missing data). Statistical analyses will be carried out using the statistical software packages SAS (V9.2) (SAS Institute Inc., Cary, North Carolina, USA), and R (V2.12) (GNU Operating System, open source).

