### Quantitative data collection

A repeated cross-sectional survey of patients’ medical charts will be carried out at all sites at five time intervals (0, 6, 12, 18 and 24 months). This survey entails randomly selecting charts of eligible patients who received primary care at the participating site at the time of the survey. This results in different patients being included at the five time points. Therefore, data on the demographic and clinical profile of patients will be obtained and controlled statistically prior to performing outcome comparisons between study groups. In the control sites, a 12-month retrospective data extraction will also be performed for each patient chart selected. In the intervention sites, a 12-month retrospective data extraction will be performed prior to the start of the intervention and up to 12 months during the intervention for each patient chart selected. This will be conducted to assess changes in patient care processes and clinical outcomes.

Data will be collected on:

1. Baseline demographic and clinical information (that is, age, sex, duration of diabetes, smoking status, comorbidity);

2. Treatment modality (that is, diet, oral agents, insulin, or insulin with oral agents), medical treatment, duration of insulin therapy;

3. Frequency and outcomes of tests or measures of HbA1c, LDL-C, TC-HDL; high density lipoprotein (HDL-C), diastolic and systolic blood pressure, glomerular filtration rate (eGFR), albumin/creatinine ratio (ACR), waist circumference, and weight.

The data will be extracted from patient charts for baseline comparisons between randomized clusters. For our primary hypothesis, we will collect HbA1c to assess the proportion of patients who achieve the recommended target for HbA1c (that is, HbA1C ≤7%) and assess change within patients in the intervention and between cluster groups. For our secondary hypothesis we will collect LDL-C, TC-HDL, and diastolic and systolic blood pressure to assess achievement of each of the recommended clinical targets (LDL-C <2.0 mmol/L, TC-HDL ratio < 4.0 and blood pressure <130/80 mmHg) and assess change within patients in the intervention and between cluster groups.

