### Statistical analysis

All sites will eventually receive the MDET intervention on an ongoing basis following the stepped wedge design, which allows us to evaluate the intervention effect utilizing both within- and between-site information while controlling for underlying time trends (for example, Hussey *et al.*, 2007)
[46]. We plan to sample 20 unique patients/charts per site per time period (1,200 in total), based on the primary hypothesis of a greater proportion of patients reaching the clinically recommended target (HbA1C ≤7%). The proposed sample size will give rise to over 80% power at a significance level of 1% (adjusting for multiple testing) assuming the between-site variation in terms of the coefficient of variation is 0.8. The minimal detectable effect size (expressed as a relative risk) based on the proposed sample is as small as 18%, for baseline proportions “p” in the range of 0.3 to 0.6 (as reported in McCrate *et al.*, 2010
[47], Harris *et al.*, 2005
[7] and Borgermans *et al.*, 2009
[15]]. For example, considering a conservative baseline proportion of *P* = 0.5 and an intraclass correlation (correlation between patients from the same site) of 0.39, we will have 80% power to detect a relative change in proportion of 18% (that is, from 0.5 to 0.59 ((0.59 to 0.5)/0.5 = 0.09/0.5 = 0.18)) attributed to the intervention over a six-month period. We will assess the sample size at the end of the 12 months, and if necessary, the sample size estimation will be adjusted according to established methods described in Chen *et al.* 2004
[48].

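### The stated mixed model for Objectives 1 and 2 has no site-by-period term, so its 1% test is too liberal if sites drift moderately around the common time trend

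*Protocol article*

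**What the plan says.** Under Quantitative data analysis, the Objective 1 outcomes are to be analysed with generalized linear mixed models "which include site as the random effect, time as a fixed effect and the intervention effect". Patient and physician covariates are added, and the section says that "GLMM will facilitate modeling all three level variances in patient outcomes", the levels being patient, physician and site. Objective 2 uses the same approach. A second method is mentioned: "we will consider the generalized estimating equations (GEE) approach, which has been suggested to be more robust to misspecification of the variance structure". The same section states that "overall Type I error will be set to 1% (instead of 5%) for all calculations of confidence intervals" and for hypothesis tests.

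Under Quantitative data collection, charts are drawn afresh at 0, 6, 12, 18 and 24 months: "This results in different patients being included at the five time points". Under Statistical analysis, the power example uses a single correlation, "an intraclass correlation (correlation between patients from the same site) of 0.39". No correlation between surveys is given.

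**The concern.** The model can be written as logit(p) = period + θ × intervention + site, plus covariates and a physician level. No random term changes with period within a site. Fixed period effects remove only the movement that all sites share. A site whose proportion at target rises or falls on its own account, for example through local prescribing or laboratory changes, has no place in the model except as chart-level noise.

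In a stepped wedge, much of the information on the intervention comes from comparing a site with itself before and after the switch, so site-specific movement enters that comparison directly. It is also not averaged away by the 20 charts in a survey, because all 20 share it. The standard error ignores this. At stake are the confidence intervals and tests for the primary outcome and for every Objective 1 and 2 outcome analysed the same way. The plan tightened its level to 1% specifically to limit false positives.

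**Working it through.** **Inputs from the article.** 20 charts per site per survey, 1,200 charts, five surveys, four start times, the Table 3 schedule, between-site coefficient of variation 0.8, P = 0.5, intraclass correlation (ICC) 0.39, level 1% (taken as two-sided). The number of sites is inferred: 1,200/(20 × 5) = 12, or 3 per start time.

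**Assumed.** The CAC, over 0.80 to 1.

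**The plan's own figures.** Between-site SD = 0.8 × 0.5 = 0.40, variance 0.16; chart variance 0.5 × 0.5 = 0.25; ICC = 0.16/(0.16 + 0.25) = 0.39. This reproduces. The claim of "over 80% power at a significance level of 1% (adjusting for multiple testing") does not: the standard stepped-wedge variance for 12 sites gives a standard error of 0.0524 for the effect and 19.5% power for 0.50 versus 0.59. That is a separate problem. It matters here only because the power statement has to be revisited anyway.

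**Type I error of the site-only model.** Let the truth contain a site-by-period variance ICC × (1 − CAC) × V, with chart variance (1 − ICC) × V / 20 per survey mean, V being the total variance. To a close approximation

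(true SE / model SE)² = 1 + 20 × ICC × (1 − CAC) / (1 − ICC),

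and the true level is 2 × [1 − Φ(2.576 / ratio)]. At ICC 0.39 and CAC 0.90: 1 + 20 × 0.39 × 0.10 / 0.61 = 2.28, ratio 1.51, 2.576/1.51 = 1.706, level about 8.8%. The exact generalized-least-squares calculation on the 12 × 5 survey means (V = 0.25) gives model SE 0.041, true SE 0.062 and level 8.7%.

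True level at nominal 1%, ICC 0.39:

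| CAC | Linear, exact | Linear, omitted variance counted as chart noise | Logistic GLMM simulated, ICC on proportion scale | Logistic GLMM simulated, ICC on latent scale |
|---|---|---|---|---|
| 1.00 | 1.0% | 1.0% | 0.9% | 1.1% |
| 0.99 | 1.5% | 1.5% | not run | 1.4% |
| 0.95 | 4.4% | 4.1% | 3.9% | 2.5% |
| 0.90 | 8.7% | 7.8% | 8.6% | 5.2% |
| 0.80 | 17.0% | 14.5% | 15.7% | 10.1% |

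The simulations used 1,000 (proportion scale) and 1,500 (latent scale) null trials per setting. Table 3 codes the first group as treated at Time 1, while its footnote calls Time 1 a baseline before the start. Coding Time 1 as all control changes the linear results by less than 0.1 percentage point.

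**Dependence on the ICC** (linear, exact):

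| ICC | CAC 0.95 | CAC 0.90 | CAC 0.80 |
|---|---|---|---|
| 0.05 | 1.2% | 1.4% | 1.8% |
| 0.10 | 1.4% | 1.9% | 3.1% |
| 0.215 (coefficient of variation 0.8 at P = 0.3) | 2.2% | 3.8% | 7.3% |
| 0.49 (coefficient of variation 0.8 at P = 0.6) | 6.5% | 13.1% | 24.0% |

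**Cost in power of modelling the drift** (variance 0.16 between sites, two-sided 1%, 0.50 versus 0.59): 19.5% at CAC 1, 10.9% at 0.95, 7.6% at 0.90, 4.9% at 0.80.

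**The case against.** The strongest reply is that the size rests on inputs the article does not supply. No CAC is stated. With total variance 0.25 and ICC 0.39, CAC 0.90 means that each site's true proportion moves independently by an SD of √(0.39 × 0.10 × 0.25) = 0.099, about 10 percentage points, at every survey; CAC 0.80 means about 14 points. The 0.39 is a worked example, not an observed value. Because eligible patients have HbA1c of at least 8%, the proportion at or below 7% might be lower than the plan's 0.3 to 0.6. At an assumed P = 0.15 the same coefficient of variation gives ICC 0.0144/(0.0144 + 0.1275) = 0.10, where the inflation is small. All of this stands, and it rules out a tempting stronger reading: that any drift at all takes the test far above 1%. At CAC 0.99 the level is only about 1.5%.

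A second reply is that the model description is not closed: a physician level, covariates and model diagnostics are also planned, and the full covariance structure could be in an analysis plan. This stands only in part. If physicians change between surveys, a physician effect could absorb some of the movement, and the calculations contain neither physicians nor covariates. But the article does state a random-effects structure, and it includes no period-within-site level.

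Third, generalized estimating equations are mentioned expressly because of variance misspecification. That is a partial safeguard: the method is only to be considered, it does not replace the primary test, and no small-sample correction is stated for about 12 sites.

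**Conclusion.** The point holds conditionally. The stated model assumes equal correlation within and between surveys over 24 months; if sites drift moderately, its standard error is too small and the 1% level is not kept. At the plan's example ICC of 0.39, with 12 inferred sites and 20 charts per survey, the true level is about 1.5% at CAC 0.99, about 4% at 0.95 (2.5% on the latent scale), 5–9% at 0.90 and 10–17% at 0.80. At ICC 0.10 or below it is about 1–3%. The CAC is an assumption throughout.

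A reader might infer that the trial's primary test is certain to be badly inflated. The article does not support that, since it says nothing about how stable sites are over time. What it does show is a large planning ICC, a strict level and a model with no protection against this departure. Should-fix, as a cheap improvement.

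**What to change.** In Quantitative data analysis, state the model for Objectives 1 and 2 as fixed categorical period, intervention effect, random site and random site-by-period (nested exchangeable correlation), with the physician level and covariates as planned and a small-sample reference such as Kenward-Roger or a t distribution. Report the within-period and between-period ICCs. Keep the site-only model as a sensitivity analysis. If generalized estimating equations are used, name the small-sample correction.

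The cost is one random term, a few sentences and no new data. The downside is wider intervals and lower power when sites drift, and slightly wider intervals when they do not. The power paragraph in Statistical analysis should therefore be restated under an assumed CAC with a range.

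One limit: a mixed model on survey-level proportions that absorbs site-by-period variation rejected in 0.4–1.4% of null trials across the settings tried. That supports the approach, but it is a linear version, not the recommended logistic model itself, whose behaviour with about 12 sites should be checked by simulation before it is fixed.

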### Experimental study design

A non-blinded, cluster-randomized trial stepped wedge design will be used (see Table 
3). Findings from such a study design have been shown to generate sound scientific evidence and may better facilitate the implementation of complex health interventions in practice
[43]. We propose to randomize clusters (that is, primary care sites) and not individuals to the intervention and control group in order to minimize contamination or treatment dissemination between study groups (intervention or control). The presence of a MDET is hypothesized to affect how PCPs care for their patients; and thus, the care patients receive within the same practice site.

**Table 3 T3:** Study design – cluster randomized control trial stepped wedge design treatment schedules

**Randomization of clusters**	**Time 1**	**Time 2**	**Time 3**	**Time 4**	**Time 5**
	**0 months***	**6 months**	**12 months**	**18 months**	**24 months**
Cluster 1	1	1	1	1	1
Cluster 2	0	1	1	1	1
Cluster 3	0	0	1	1	1
Cluster 4	0	0	0	1	1

“*” represents baseline data collection across all sites prior to cluster 1 starting the intervention;

“0” represents control or existing treatment/standard care at primary care sites; “1” represents the MDET intervention; each column represents a data collection point.

Because all PCPs who expressed an interest in this study are eager to have a MDET on site, we plan to use a stepped wedge design to sequentially roll out the intervention. The time at which each cluster begins the intervention is randomized to one of the four roll-out periods (0, 6, 12, and 18 months). The randomization times are separated by six months to allow for assessment of the primary outcome (that is, HbA1c) within a reasonable time after implementation of the intervention

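### With only 12 sites implied, the supporting GEE analysis needs a small-sample correction: in its usual form a nominal 1% test has a true error rate of about 3 to 5%

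*Protocol article*

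**What the plan says.** Under Quantitative data analysis, the protocol article tests the clinical outcomes, HbA1c target attainment among them, with a GLMM that has a random site effect, fixed time and an intervention term. It then adds: "we will consider the generalized estimating equations (GEE) approach, which has been suggested to be more robust to misspecification of the variance structure". The same section fixes the error rate for everything it has described: "overall Type I error will be set to 1% (instead of 5%) for all calculations of confidence intervals and for testing the various hypotheses". The stated purpose is protection against false positives from multiple testing.

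The number of sites is not given, but it follows from other statements. Statistical analysis says: "We plan to sample 20 unique patients/charts per site per time period (1,200 in total". Quantitative data collection has the chart survey "carried out at all sites at five time intervals (0, 6, 12, 18 and 24 months". Under Experimental study design, each cluster's start is "randomized to one of the four roll-out periods (0, 6, 12, and 18 months".

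**The concern.** GEE is added for one reason: its inference should survive a wrong assumption about the correlation between patients at a site. The sandwich variance provides that protection, and it is a large-sample property in the number of clusters, not the number of patients. With few clusters the usual sandwich estimate is biased downwards and is itself variable. A normal reference allows for neither.

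The 1% level is meant to cover the GEE tests and intervals as well. If GEE is run in its usual form at this size, its p-values are too small and its intervals too narrow. If the two methods disagreed, a reader told that GEE is the more robust one could give more weight to the result with the poorer error control.

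**Working it through.** **Inputs from the article**
- 20 charts per site per survey and 1,200 charts in total (Statistical analysis).
- Five surveys at all sites (Quantitative data collection).
- Four start times (Experimental study design and Table 3).
- Error rate 1% (Quantitative data analysis).
- Planning values: "considering a conservative baseline proportion of *P* = 0.5 and an intraclass correlation (correlation between patients from the same site) of 0.39", with a between-site coefficient of variation of 0.8 (Statistical analysis).

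**Assumptions**
- Three sites per start time (12 / 4).
- Two-sided tests.
- Uncorrected sandwich with a normal reference as the usual form of GEE.

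**Step 1: number of sites.** 1,200 / (20 x 5) = 12.

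**Step 2: the article's intraclass correlation.** The between-site SD is 0.8 x 0.5 = 0.4, so the variance is 0.16. The within-site variance is 0.5 x 0.5 = 0.25. Then 0.16 / (0.16 + 0.25) = 0.390, which reproduces the stated 0.39. (The stated 80% power does not reproduce from the same inputs. That is a separate matter, and nothing here depends on it.)

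**Step 3: error rate of GEE with no true effect.** Binary outcomes were simulated for 12 sites, five surveys and 20 charts, with beta-distributed site proportions. A logistic GEE with survey and intervention terms was fitted. The four main settings had baseline 0.5 and 12,000 trials each. KC is Kauermann-Carroll, MD is Mancl-DeRouen, and t(10) uses sites minus two. The last five columns give rejection rates of the nominal 1% test.

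| Working correlation, ICC | Mean robust SE / true SD | Usual SE, normal | Usual SE, t(10) | KC, normal | KC, t(10) | MD, t(10) |
|---|---|---|---|---|---|---|
| Exchangeable, 0.39 | 0.87 | 4.1% | 1.5% | 2.7% | 0.9% | 0.6% |
| Exchangeable, 0.05 | 0.87 | 4.35% | 1.7% | 2.9% | 1.0% | 0.5% |
| Independence, 0.39 | 0.86 | 4.5% | 1.8% | 3.0% | 1.2% | 0.8% |
| Independence, 0.05 | 0.87 | 4.5% | 1.9% | 3.0% | 1.1% | 0.7% |

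The Monte Carlo standard error at 4.1% is sqrt(0.041 x 0.959 / 12,000) = 0.18 percentage points. At a nominal 5% the usual test rejects in 10.5 to 11.6% of trials.

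**Step 4: where the inflation comes from.** With an SE of 0.872 of its true value, the effective critical value is 2.576 x 0.872 = 2.25, which is a two-sided error of about 2.5%. The rest, up to 4.1%, arises because the SE is itself estimated from 12 clusters. The table shows the same: correcting only the SE (KC with a normal reference) or only the reference (usual SE with t(10)) leaves 1.5 to 3.0%. Both are needed.

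**Step 5: stability.** Across 28 settings (ICC 0.05, 0.1 or 0.39; baseline 0.3 or 0.5; added site-by-period variation; both working correlations; the first group exposed or not at time 0) the usual test rejected in 3.3 to 5.3% of trials, and the SE ratio was 0.84 to 0.90. Separate runs with normal site effects on the logit scale (eight settings, 1,500 trials each) gave 3.3 to 4.9%.

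**Step 6: dependence on the number of sites.** At ICC 0.05 with exchangeable correlation the rate falls to 2.9% at 20 sites, 1.6% at 40 and 1.2% at 80. The small number of sites is the cause.

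**The case against.** **The uncorrected variance is not in the text.** The article names no variance estimator, reference distribution or working correlation for GEE. Such details usually sit in an analysis plan, which is not shown. This stands: the absence of a correction is not itself an error, and a correction specified elsewhere would remove the problem. What remains is that the article promises a 1% rate for these analyses, and GEE in its usual form cannot deliver it at the size the article fixes.

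**The GLMM is already the test.** A reader might infer that the choice between methods is open, so that the smaller p-value could be picked, or that GEE undoes the 1% safeguard for the primary hypothesis. The text does not support either reading. It assigns the clinical outcomes to the GLMM and brings GEE in only as an addition to be considered.

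**The robustness statement is not false.** It is true as a large-sample property, and insensitivity to the variance structure can be seen even here. In a comparison with 12 sites (800 null trials per setting, Monte Carlo error up to about 0.8 points), rejection at nominal 1% was:
- without site-by-time variation: GLMM 0.6 to 0.9%, GEE 3.9 to 4.0%;
- site-by-time SD 0.25 (logit scale): GLMM 1.9 to 2.1%, GEE 2.8 to 3.4%;
- site-by-time SD 0.5: GLMM 5.0 to 6.1%, GEE 3.8 to 4.0%.

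The GEE error changes little as the variance structure departs from the model, but it sits at about three to four times the nominal level throughout. Nor do these figures show the planned GLMM to be defective: its rate rises only with an assumed site-by-time variation, for which the article gives no figure.

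**The site count could change.** The article plans to reassess the sample size at 12 months. It does not say that sites would be added.

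**Conclusion.** The point holds in a limited form. At the 12 sites implied by the article, GEE with the usual sandwich standard errors and a normal reference has standard errors about 10 to 15% too small. Its true error rate is about 3 to 5% at a nominal 1%, so a nominal 99% interval covers roughly 95 to 97%. This concerns the supporting GEE analysis. It would touch the primary conclusion only if GEE replaced the GLMM.

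The conclusion rests on the derived site count, an even split over the four start times, two-sided tests and the uncorrected form of GEE, which the article neither states nor rules out. The size of the inflation hardly depends on the intraclass correlation, baseline proportion or working correlation tried.

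**What to change.** Add two statements to the analysis section or the analysis plan:
1. The GLMM decides the primary hypothesis, and GEE is a sensitivity analysis.
2. GEE is reported with a small-sample-corrected sandwich variance, for example Mancl-DeRouen or Kauermann-Carroll, and a t reference with degrees of freedom based on the number of sites (10 in the simulations).

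In the 12,000-trial runs this brought the 1% test to 0.9 to 1.2% with Kauermann-Carroll and 0.5 to 0.8% with Mancl-DeRouen. The latter is somewhat conservative. The cost is a sentence or two, a change in how the GEE variance is computed, and somewhat wider GEE intervals. Neither the design nor data collection changes.

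Small-sample degrees of freedom for the GLMM, or a permutation test over the randomised start times, would be an optional precaution and does not answer a demonstrated fault.

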**Methods/design:**

This study will use a non-blinded, cluster-randomized controlled trial stepped wedge design to evaluate the Mobile Diabetes Education Teams' intervention in improving patient clinical and care process outcomes. A total of 1,200 patient charts at participating primary care sites will be reviewed for data extraction. Eligible patients will be those aged ≥18, who have type 2 diabetes and a hemoglobin A1c (HbA1c) of ≥8%. Clusters (that is, primary care sites) will be randomized to the intervention and control group using a block randomization procedure within practice size as the blocking factor. A stepped wedge design will be used to sequentially roll out the intervention so that all clusters eventually receive the intervention. The time at which each cluster begins the intervention is randomized to one of the four roll out periods (0, 6, 12, and 18 months). Clusters that are randomized into the intervention later will act as the control for those receiving the intervention earlier. The primary outcome measure will be the difference in the proportion of patients who achieve the recommended HbA1c target of ≤7% between intervention and control groups. Qualitative work (in-depth interviews with primary care physicians, MDET educators and patients; and MDET educators’ field notes and debriefing sessions) will be undertaken to assess the implementation process and effectiveness of the MDET intervention.

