### Scientific hypothesis

We hypothesize that the MDET intervention results in the following outcomes at 12 months:

(i) An improvement in patient clinical outcomes, primarily an increase, or greater proportion, of patients in the intervention group who are at target for HbA1c (≤7%) compared to patients in the control group.(Secondary hypothesis: an increase, or greater proportion, of patients in the intervention group who are at target for low-density lipoprotein (LDL-C) ≤2.0 mmol/L, total cholesterol-high density lipoprotein ratio (TC-HDL ratio) < 4.0, and blood pressure ≤ 130/80 mmHg, compared to patients in the control group).

(ii) An increase in the proportion of PCPs performing patient care processes, according to the Canadian clinical practice guidelines for the management of diabetes, in the intervention group compared to the control group.

(iii) An increase in the proportion of referrals to and patients’ utilization of DEPs in the intervention group compared to one year prior to the start of the intervention.

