The proportion of patient care processes completed by PCPs over a one-year period (that is, the percentage of patients with tests for HbA1c, blood pressure, lipid profile, screening for nephropathy (ACR and eGFR), foot exams, referrals for dilated retinal exams, and provisions for or recommendations of the flu vaccine) according to clinical practice guidelines will also be collected from patient charts and compared across study groups. We also plan to document and descriptively examine changes to medication (that is, change in drug, drug dose, and addition of another drug) to assess intensification of medical management and whether the diabetes educators had an influence on PCP practices. Descriptive information (that is, sex, age, years practicing) will be collected for each PCP to further assess differences in patient care processes between study groups.

We will also calculate the percentage of patient referrals by PCPs to hosting DEPs and the onsite MDET and compare this to patients’ actual attendance at DEPs and scheduled MDET appointments. The referral rate to DEPs will be compared to the percentage of referrals from participating PCPs and their patients’ attendance at DEPs a year prior to the start of the intervention. Characteristics available in patient medical charts (that is, sex, age, duration of diabetes, clinical information and so on) will be reviewed and compared between those who were and were not referred to the MDET to better understand PCP referral practices. The number of MDET appointments planned for each patient and the number of MDET visits attended will be collected during the intervention period to examine uptake of the MDET intervention.

Various characteristics of team collaboration will be measured using the Collaborative Practice Assessment Tool (CPAT) Version 2

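### The article calls 1% the overall Type I error but applies 1% to every test, so across its 13 hypothesised outcomes the family-wise error is not 1%

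*Protocol article*

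**What the plan says.** Three places in the Protocol article bear on this.

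- **Quantitative data analysis:** "overall Type I error will be set to 1% (instead of 5%) for all calculations of confidence intervals and for testing the various hypotheses". The reason given is protection against false positives from multiple testing.
- **Statistical analysis:** the sample is said to give "over 80% power at a significance level of 1% (adjusting for multiple testing"), for the primary hypothesis. The level used to size this one test equals the level called overall.
- **Scientific hypothesis and Quantitative data collection:** these set out what is tested. The abstract names one primary outcome: "The primary outcome measure will be the difference in the proportion of patients who achieve the recommended HbA1c target of ≤7"%. A secondary hypothesis adds the proportions "at target for low-density lipoprotein (LDL-C) ≤2.0 mmol/L, total cholesterol-high density lipoprotein ratio (TC-HDL ratio) < 4.0, and blood pressure ≤ 130/80 mmHg". Hypothesis (ii) is "An increase in the proportion of PCPs performing patient care processes, according to the Canadian clinical practice guidelines for the management of diabetes". The individual processes are listed under Quantitative data collection and "will also be collected from patient charts and compared across study groups". Hypothesis (iii) expects increases in referrals to diabetes education programs (DEPs) and in their use.

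The article labels outcomes as primary and secondary. It does not say that one is tested before another, that a later test depends on an earlier result, or that the 1% is divided.

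**The concern.** An overall Type I error is normally read as the probability of at least one false rejection across the whole set of tests. A common level of 1% for each test does not give an overall 1% unless the tests are ordered or perfectly correlated. As written, the sentence claims a property that the stated procedure does not deliver.

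The risk lies mainly with the secondary, care-process and DEP outcomes. If a single process measure reached, say, p = 0.008, a report following this text could call it significant with the overall error held at 1%. The chance that some outcome in the set would do so by luck is several times larger. The Discussion says the results are meant to inform health service policy makers, so the strength attached to such a finding matters.

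**Working it through.** **Step 1. Count the outcomes hypothesised to improve.**

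| Group | Outcomes | Count | Source |
|---|---|---|---|
| Clinical targets | HbA1c, LDL-C, TC-HDL ratio, blood pressure | 4 | Scientific hypothesis (i) |
| Care processes | HbA1c test, blood pressure, lipid profile, nephropathy screening, foot exam, retinal referral, flu vaccine | 7 (8 if ACR and eGFR are separate) | Scientific hypothesis (ii); Quantitative data collection |
| DEP outcomes | referrals, utilization | 2 | Scientific hypothesis (iii) |

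Total: 4 + 7 + 2 = 13, or 14 with ACR and eGFR apart. Medication changes are left out because the article examines them only descriptively.

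**Step 2. The article's figure.** An error of 1% is reproduced for k = 1 test: 1 − 0.99¹ = 0.01. It is therefore correct for the primary test taken alone.

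**Step 3. Independent tests at 1% each, all null hypotheses true.** The family-wise error is 1 − (1 − 0.01)^k.

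- k = 13: 1 − 0.99¹³ = 1 − 0.8775 = 12.25%
- k = 14: 1 − 0.99¹⁴ = 1 − 0.8687 = 13.1%
- Bonferroni bound, valid under any dependence: 13 × 0.01 = 13%, and 14 × 0.01 = 14%

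**Step 4. Correlated tests.** The article gives no correlation between test statistics, so a range is shown. For k two-sided normal statistics with common correlation ρ and c = 2.576, the family-wise error is

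1 − ∫ φ(u) [Φ((c − √ρ·u)/√(1−ρ)) − Φ((−c − √ρ·u)/√(1−ρ))]^k du.

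| Assumed ρ | 13 tests | 14 tests |
|---|---|---|
| 0 | 12.25% | 13.1% |
| 0.3 | 10.8% | 11.5% |
| 0.5 | 8.8% | 9.3% |
| 0.7 | 6.3% | 6.6% |
| 0.8 | 4.9% | 5.1% |
| 0.9 | 3.4% | 3.5% |

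The rate falls as ρ rises but reaches 1% only at ρ = 1. Two-sided tests are assumed because the article does not state sidedness. The independent values in Step 3 do not depend on that assumption.

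**Step 5. What the 1% level does achieve.** At 5% per test, 13 independent tests give 1 − 0.95¹³ = 1 − 0.5133 = 48.7%. Moving to 1% cuts this to 12.25%, about a quarter.

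**Step 6. Would a testing order reconcile the sections?** Yes. If HbA1c is tested first at 1% and nothing else is tested unless it succeeds, a true primary null is falsely rejected at most 1% of the time, and no other error can occur without that rejection. If the primary null is false, the first error must arise in a later step, and Holm at 1% within that step bounds it at 1%, provided that each step opens only when every test in the step before it has been rejected. The overall error is then 1% and the primary test keeps its full 1%.

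**The case against.** The strongest reply is that 'overall' is loose wording for a stricter common level. The 5% it replaces is the ordinary per-test level, confidence intervals take their coverage one at a time, and the Statistical analysis section speaks simply of a significance level. On that reading the two sections agree and no family-wise rate is promised. The article also names one primary outcome and labels a secondary hypothesis, never calls the 13 outcomes one confirmatory family, and may leave a testing order to a document not shown.

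Part of this stands. The absence of an order from a condensed article is not in itself a fault, and the primary test's error is 1% on either reading. But the point rests on what the sentence says: it fixes one level for every test, ties it to multiple testing and calls it overall. If a common per-test level is meant, the word is wrong. Labels of primary and secondary do not by themselves create a testing order.

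A reader might infer more than the documents support:

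- **That the two sections cannot both hold.** They can, under a fixed sequence at 1% (Step 6).
- **That a literal overall 1% forces the primary to about p < 0.0008.** This is 0.01/13 and applies only to an equal split over 13 tests, which the article never specifies.
- **That the error rate is about 9%.** This needs an assumed correlation near 0.5. Nor is 12% a ceiling, since the bound for 13 tests is 13%.
- **That the primary test gives up power for nothing.** The 1% level cuts the independent rate from about 49% to about 12%, and the article claims its power at 1%, so the stricter level is already in its stated sample size. Whether that power figure reproduces is a separate question with no bearing on multiplicity.

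**Conclusion.** The concern holds in a limited form. The article attaches the word 'overall' to a level that is overall only if a testing order or a split exists, and it states neither. For 13 outcomes at 1% each, the family-wise error is 12.25% under independence and 3.4% at a common correlation of 0.9, with an upper bound of 13%. That is roughly 3 to 12 times the stated 1%.

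These figures assume that all 13 null hypotheses are true, that each listed care process is tested separately, and, for the correlated values, equal correlation and two-sided tests. A smaller family would lower the numbers without rescuing the claim: the four clinical targets alone give 1 − 0.99⁴ = 3.9% if independent. The conclusion on HbA1c is not threatened. What needs correcting is the claim made for the set of outcomes. It should be corrected, but it does not undermine the design.

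**What to change.** Amend the sentence in Quantitative data analysis in one of two ways.

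**(a) Make 'overall 1%' true.** State that HbA1c ≤7% is tested first at 1%. Only if it is significant, test LDL-C, TC-HDL ratio and blood pressure by Holm at 1%. Only if all three are significant, test the care-process and DEP outcomes by Holm at 1%. Say whether ACR and eGFR count as one outcome or two. Describe the 99% confidence intervals as having individual, not simultaneous, coverage. The primary test's level and planned power do not change. The cost falls on the later outcomes: Holm's first threshold is 0.01/3 = 0.0033 in the second step and 0.01/9 = 0.0011 in the third, and a failed step closes those after it. If that chain is too strict, a single Holm step over the remaining 12 outcomes, starting at 0.01/12 = 0.0008, also holds the overall error at 1%.

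**(b) Describe 1% as what it is.** Drop 'overall', call 1% a per-test level, and state that the family-wise error across all outcomes is not controlled at 1%. This costs no power, but significant secondary, process and DEP results must then be reported without that protection.

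Both are wording changes that need no new data. Moving the primary test to 5%, or relabelling the process and DEP outcomes as exploratory, is optional and not part of this correction.
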